### Sample size calculation

Previous studies report that respiratory critical events during paediatric airway management occur with an incidence ranging from 0.28% to 6%.^4^ We calculated the sample size using the Wilson method. To adopt a conservative approach, we assumed an expected event rate between 1% and 0.5% for the less represented age groups and explored several precision scenarios, with the half-width of the 95% confidence interval ranging from 7% to 9.5% of the estimated incidence. Selected combinations of incidence and precision, along with the corresponding sample sizes, are shown in Table 2. Specifically, our target was to obtain a 95% confidence interval of 0.9–1.1% around an expected incidence of 1%. To further ensure robustness, we calculated a conservative scenario based on a 0.5% incidence and 8.5% precision, resulting in a required sample size of approximately 105 000 patients. The number of participating centres will depend on each centre’s expected caseload during the 3-month observational window. If the required sample size is not achieved within the planned 24-month recruitment period, the steering committee may either extend recruitment or conclude enrolment and analyse the accumulated data, depending on the number of recorded events and the remaining available resources. All sample size computations were performed using the R package binomSamSize.^15^

**Table 2 tbl2:** Sample size corresponding to the different scenarios of precision, considering the combinations with an event rate of 1% or 0.5% and a precision level ranging from 7% to 9.5% of the expected event rate.

Precision level	Sample size	
	1% event rate	0.5% event rate
7% of the event rate	77 702	156 099
7.5% of the event rate	67 650	136 044
8.5% of the event rate	52 714	105 897
9.5% of the event rate	42 215	84 845

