Where earlier studies have reported critical events in broad terms, often limited to severe outcomes such as cardiac arrest or death, the CRICKET study will address this gap by prospectively capturing detailed, standardised data on a vast number of airway-related critical events during tracheal intubation in children up to 16 yr of age. The inclusion of centres with diverse geographic and economic backgrounds enhances the generalisability and external validity of the study's findings.

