### Statistical analysis

A descriptive analysis of the data will be carried out, using counts and percentages to summarise categorical data and median (interquartile range) to summarise continuous data.

The incidence of critical events will be estimated and reported together with a 95% confidence interval. Furthermore, critical event incidence will be provided for different age categories, operator’s experience, operator’s speciality, and centre volume.

In terms of risk factor analysis, a univariable and multivariable mixed-effect logistic regression model will be computed based on possible predictors, which include for example age (≤12 months), weight (≤10 kg), number of attempts (more than two), presence of comorbidities (ASA score ≥3), comorbidity related to airway management (e.g. relevant syndromes), expected difficult intubation, type of anaesthesia induction (i.v. or inhalation), no neuromuscular blocking agent given, airway surgery or ears, nose, throat (ENT) surgery, and experience level of the person performing tracheal intubation. Appendix 1 lists the relevant factors used for primary and secondary analyses. Goodness-of-fit, calibration, discriminatory capacity, and predictive skill of the regression models will be assessed using Nagelkerke pseudo-*R*^2^, calibration belts, area under the receiver operating characteristic curve (AUROC), and Brier Score, respectively.

The target sample size for CRICKET is informed by statistical considerations and the practical constraints of conducting a large, multinational observational study. Although the sample size calculation indicates that approximately 105 000 cases are required to estimate an event rate of 0.5–1% with acceptable precision, the achievable enrolment also depends on centre capacity, case volume, and the coordinated activation of participating sites across multiple jurisdictions. Recruitment will therefore proceed sequentially from January 2024 to December 2025, with each centre contributing a consecutive 3-month sampling window once local approvals and resources are in place. If the required sample size is not reached by the end of 2025, the steering committee may extend the recruitment period or, alternatively, close enrolment and proceed with analysis of the accrued data, depending on the number of events captured and the resources remaining.

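### The sample size and its stated precision treat cases as independent although whole centres are sampled, so the precision is optimistic by an amount the article does not let one fix

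*Protocol article*

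**What the plan says.** The Sample size calculation section states "We calculated the sample size using the Wilson method" and "All sample size computations were performed using the R package binomSamSize". The scenarios have a stated precision "with the half-width of the 95% confidence interval ranging from 7% to 9.5% of the estimated incidence", at rates of 1% and 0.5%. The target is a 95% interval of 0.9–1.1% around 1%. The figure of about 105,000 comes from the next step: "we calculated a conservative scenario based on a 0.5% incidence and 8.5% precision". No intracluster correlation or design effect is mentioned. The number of centres is left to follow from their caseloads.

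The Abstract, Study design and Statistical analysis sections have each centre record all eligible cases in one consecutive three-month window. The introduction, just before Methods, adds: "The inclusion of centres with diverse geographic and economic backgrounds enhances the generalisability and external validity".

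For the primary result, the Statistical analysis section says only "The incidence of critical events will be estimated and reported together with a 95% confidence interval". It names no interval method. For risk factors, "a univariable and multivariable mixed-effect logistic regression model will be computed based on possible predictors".

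The Results section projects about 50,000 patients by the end of 2025, when recruitment stops.

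**The concern.** Cases from one hospital share staff, case mix, equipment and reporting habits. When whole centres are sampled and the result is meant to apply beyond them, the precision of a pooled incidence depends on the number of centres and the spread of their sizes as well as on the number of cases. A formula for independent cases ignores this.

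The article itself gives reasons to expect differences between centres. It calls practice heterogeneous and recruits academic and non-academic, children's and mixed hospitals across continents. It counts an event only if the treating provider documents it, with research staff checking where they are available.

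The primary result is one proportion with its interval, so the planned precision is the main design quantity of the study. It also bears on the choice, left to the steering committee, to extend or close recruitment according to events recorded and resources.

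**Working it through.** **1. Reproducing Table 2.** The Wilson half-width is z√n/(n+z²) × √(p(1−p) + z²/(4n)), with z = 1.96. Setting it equal to the stated fraction of p and solving for n, with no design effect, gives:

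| Half-width, % of p | 1% rate: solved / Table 2 | 0.5% rate: solved / Table 2 |
|---|---|---|
| 7 | 77,702 / 77,702 | 156,195 / 156,099 |
| 7.5 | 67,699 / 67,650 | 136,087 / 136,044 |
| 8.5 | 52,726 / 52,714 | 105,991 / 105,897 |
| 9.5 | 42,228 / 42,215 | 84,889 / 84,845 |

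All eight agree within 0.1%, so the table contains no allowance for centre.

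**2. How much clustering the target can absorb.** A half-width of 0.1 percentage point at p = 1% needs n = 38,120 independent cases. The largest tolerable design effect is the actual n divided by this:
- 105,000 / 38,120 = 2.75
- 50,000 / 38,120 = 1.31

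For equal clusters of size m, the design effect is 1 + (m − 1) × ICC, where ICC is the intracluster correlation. Assume 200 centres:
- At 50,000, m = 250 and the limit is ICC = 0.31/249 ≈ 0.00125. As a between-centre standard deviation of the true rate this is √(0.00125 × 0.01 × 0.99) ≈ 0.35 percentage points around 1%.
- At 105,000, m = 525 and the limit is ICC = 1.754/524 ≈ 0.0033.

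**3. Half-widths under assumed values.** None of the following inputs is in the article: 200 centres, a standard deviation (SD) of centre log-odds of 0.3 to 0.7, and a coefficient of variation (CV) of centre size of 0 or 1. With p = 1%:
- ICC = p(exp(SD²) − 1)/(1 − p), giving 0.00095, 0.00287 and 0.00639 for SD 0.3, 0.5 and 0.7.
- Design effect = 1 + ((1 + CV²)m − 1) × ICC.
- Half-width = the Wilson half-width at n divided by the design effect.

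| SD | CV | 50,000: design effect | 50,000: half-width (points) | 105,000: design effect | 105,000: half-width (points) |
|---|---|---|---|---|---|
| none | – | 1.00 | 0.087 | 1.00 | 0.060 |
| 0.3 | 0 | 1.24 | 0.097 | 1.50 | 0.074 |
| 0.3 | 1 | 1.48 | 0.106 | 2.00 | 0.085 |
| 0.5 | 0 | 1.71 | 0.114 | 2.50 | 0.095 |
| 0.5 | 1 | 2.43 | 0.136 | 4.01 | 0.121 |
| 0.7 | 0 | 2.59 | 0.141 | 4.35 | 0.126 |
| 0.7 | 1 | 4.19 | 0.179 | 7.70 | 0.168 |

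At 105,000 the 0.1-point target is met in three of the six clustered settings; at 50,000 it is met in one.

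**4. What a Wilson interval would do if carried into the analysis.** Its approximate coverage is 2Φ(1.96/√design effect) − 1. At 50,000 this runs from about 92% (design effect 1.24) to about 66% (4.19). Simulation with 200 centres and size CV 1 gave 88%, 78% and 68% for SD 0.3, 0.5 and 0.7. These figures are conditional, because the article does not say that this interval will be used.

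**The case against.** The strongest reply has four parts.

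- **The analysis interval is not specified.** A reader might infer that the primary interval will be a Wilson interval that ignores centre, and so will under-cover. The article does not say this. Wilson is named only for the sample size, and the interval method may be in an analysis plan that is not shown. A reader might likewise infer that subgroup intervals will be too narrow, but the text promises subgroup incidences and mentions no intervals for them. This part stands: the coverage figures are a warning and do not describe the plan.
- **The size of the loss is assumed.** This also stands. At 105,000 the target survives a design effect of about 2.75 and is met in several plausible settings. With 500 centres, SD 0.5 and size CV 1 the half-width there is 0.089 points. A claim that the study will miss its target, or that the interval is badly wrong, goes beyond the documents.
- **The target might be the participating centres only.** Between-centre variance would then not enter, and a Wilson interval would be adequate. The centres are volunteers from an open call, and a cluster-robust interval does not cure that selection. However, the article claims generalisability, so the wider target is the natural reading.
- **The study is descriptive and recruitment is closing.** No test or decision threshold hangs on the interval, so this is no reason to recruit more. The precision still has to be reported correctly.

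**Conclusion.** The point holds for the sample size and the stated precision. Table 2, the figure of about 105,000 and the 0.9–1.1% target all assume independent cases, while the design samples whole centres and the article looks beyond them. For any positive intracluster correlation the stated precision is optimistic.

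The amount cannot be fixed from the article. The margin is comfortable at 105,000 (design effect up to about 2.75) and thin at the projected 50,000 (about 1.31). The half-width ranges in the working rest on 200 centres, SD of centre log-odds 0.3–0.7, size CV 0–1 and a 1% rate; other values would move them.

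The documents do not show that the primary interval ignores centre. This is a moderate point about stated precision, to be settled before the database is locked.

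**What to change.** In the Sample size calculation section, add the precision with a design effect over a range of intracluster correlations, numbers of centres and coefficients of variation of centre size, for both 105,000 and the projected 50,000. The intracluster correlation can be estimated from the cases already entered, about 25,000 by May 2025. Recruitment need not be enlarged.

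In the Statistical analysis section, state that the primary incidence, and any subgroup incidence given with an interval, is reported with a centre-robust 95% interval: either a cluster-robust interval on the logit scale or a bootstrap that resamples centres. This rules out carrying the Wilson interval over from the sample size section, where it would under-cover if centres differ.

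The cost is one paragraph, a few lines of code and a wider reported interval. The change does not address selection of volunteer centres, which should remain a stated limitation.

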**Results:**

The CRICKET study started in January 2024 and is currently ongoing. By May 2025, around 25 000 patients were entered into the database, with an estimated 50 000 patients by the end of 2025. Because of the observational nature of the study and the extensive international involvement and effort, continuing the study or analysing the existing data will depend on available resources and exact incidence of critical events.

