## Results

The CRICKET study is currently ongoing. In May 2025, around 25 000 patients were entered into the database, with a projected 50 000 patients by the end of 2025. Due to the observational nature of the study and the extensive international involvement and effort, the steering committee decided to stop recruiting at the end of 2025 and proceed with database cleaning, subsequent statistical analysis, and publication.

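### The article keeps 105 000 as the required size although recruitment is to stop at a projected 50 000; its two precision criteria then disagree on whether that is enough, and the achievable precision is not stated

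*Protocol article*

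**What the plan says.** The Sample size calculation section bases the size on the width of a confidence interval: "We calculated the sample size using the Wilson method", "with the half-width of the 95% confidence interval ranging from 7% to 9.5% of the estimated incidence". It introduces the rates with "we assumed an expected event rate between 1% and 0.5% for the less represented age groups". Two criteria follow.

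- The named target: "Specifically, our target was to obtain a 95% confidence interval of 0.9–1.1% around an expected incidence of 1" per cent.
- The scenario that sets the size: "we calculated a conservative scenario based on a 0.5% incidence and 8.5% precision, resulting in a required sample size of approximately 105 000 patients". The matching cell of Table 2 is 105 897.

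Four places then bear on how many patients there will be.

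- Abstract, Methods: 105 000 is the aim.
- Statistical analysis: approximately 105 000 "cases are required to estimate an event rate of 0.5–1% with acceptable precision". Both this section and the sample size section let the steering committee either prolong enrolment or close it if the number is not reached.
- Abstract, Results: about 50 000 are expected by the end of 2025, and "continuing the study or analysing the existing data will depend on available resources and exact incidence of critical events".
- Results section of the main text: the same 50 000 is projected, and "the steering committee decided to stop recruiting at the end of 2025 and proceed with database cleaning".

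No section states the precision that 50 000 would give.

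**The concern.** The primary outcome is an incidence reported with its 95% confidence interval, so precision is the only justification offered for the size. The plan has two precision criteria and does not say which one decides adequacy. This would be harmless at 105 000, which satisfies the named target easily and was sized for the 0.5% scenario. At about 50 000 it is not harmless, because one criterion may be met and the other missed.

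A reader who takes 105 000 as the requirement will conclude that the study stopped at less than half its necessary size. A reader who takes the named target may conclude that it has enough. A reader of the abstract alone will not learn that the stop has been decided. The article also goes on presenting 8.5% precision at 0.5% as the basis of the design.

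**Working it through.** **Inputs.** Wilson interval, two-sided 95% (z = 1.96), precision defined as half-width, rates of 1% and 0.5%, Table 2 and the named target: all from the Sample size calculation section. Projected 50 000: Results section. Cases are treated as independent, as in the plan's own calculation.

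**Formulas.** For rate p and size n:

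- half-width h = z·√(p(1−p)/n + z²/(4n²)) / (1 + z²/n)
- centre c = (p + z²/(2n)) / (1 + z²/n)
- interval c ± h

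**Step 1: reproduce Table 2.** Smallest n with h no larger than the stated fraction of p:

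| Precision | 1%: plan | 1%: recomputed | 0.5%: plan | 0.5%: recomputed |
|---|---|---|---|---|
| 7% | 77 702 | 77 703 | 156 099 | 156 196 |
| 7.5% | 67 650 | 67 699 | 136 044 | 136 088 |
| 8.5% | 52 714 | 52 727 | 105 897 | 105 992 |
| 9.5% | 42 215 | 42 229 | 84 845 | 84 889 |

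Every cell agrees within 0.1%. The table is sound.

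**Step 2: the size implied by the named target.** An interval of 0.9–1.1% around 1% has a half-width of 0.1 points, 10% of the rate.

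- By half-width alone (h ≤ 0.1 points), n = 38 120. The Wilson centre lies slightly above p, however, and the interval at that size is 0.905–1.105%, so the upper limit passes 1.1%.
- For both limits to lie inside 0.9–1.1%, n must be about 41 800. Table 2's 9.5% row (42 215) gives 0.909–1.0995%, so that row meets the target.

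On either reading the named target needs roughly 38 000 to 42 000 cases: 38 120/105 000 = 36% to 42 215/105 000 = 40% of the stated requirement.

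**Step 3: what 105 000 gives.** At 1%, h = 0.060 points (6.0% of the rate; 0.942–1.062%). At 0.5%, h = 0.0427 points (8.5%; 0.459–0.545%). So 105 000 belongs to the 0.5% criterion and far exceeds the named target.

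**Step 4: what 50 000 gives.**

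- p = 1%: √(0.0099/50 000 + 3.8415/(4 × 50 000²)) = 0.0004454, so h = 0.000873, or 0.087 points. Interval 0.917–1.091%; half-width 8.7% of the rate. The named target is met.
- p = 0.5%: √(0.004975/50 000 + 3.8415/(4 × 50 000²)) = 0.0003160, so h = 0.000619, or 0.062 points. Interval 0.442–0.566%; half-width 12.4% of the rate, against 8.5% planned and 9.5% in the loosest row of Table 2. Even 10% at this rate would need 76 630.

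**Step 5: room for clustering at 1%.** 50 000/38 120 = 1.31 by half-width and 50 000/41 800 = 1.20 with both limits inside. The named target therefore survives a variance inflation of about 1.2 to 1.3, and no more.

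**The case against.** The strongest reply is that nothing is miscalculated or concealed. Table 2 reproduces, the article openly attributes 105 000 to a separate conservative scenario, closing below target was permitted in advance, and the Results section discloses the decision. The primary result will carry its actual interval whatever the plan says. All of this stands, and it rules out several stronger readings.

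- *That 105 000 is an arithmetic error for the 0.9–1.1% target.* The article never says it is the size for that target, and choosing a larger size for robustness is legitimate.
- *That 38 100 is the correct size.* It meets the half-width criterion but not the printed upper limit.
- *That the stop breaks the plan.* It exercises an option the plan contains.
- *That 50 000 is out of reach.* Extrapolating the 25 000 entered by May 2025 assumes constant accrual, whereas centres are activated sequentially and no monthly figures are given.
- *That the precision fails in every age group.* The article gives no stratum sizes, cites incidences up to 6%, and promises only that incidence will be reported by age category. Any figure per age group would rest on an assumed group size.

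The reply does not answer the narrower point. The abstract and the Results section describe the same decision differently, 105 000 is still called required, and the precision at the decided stop appears nowhere.

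**Conclusion.** The point holds as a failure to fix the governing criterion and to carry the stopping decision through the text. At about 50 000 independent cases the named 1% target is met (0.92–1.09%, 8.7% of the rate), while the 0.5% criterion behind 105 000 is not (0.44–0.57%, 12.4% instead of 8.5%, an interval about 0.062/0.0425 = 1.46 times as wide as planned). The article therefore states a size and a precision it does not expect to deliver, and its own criteria disagree on whether the study is adequate.

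The age-group wording adds an ambiguity: the rates are described as those of sparse age groups, but Table 2's sizes are applied to the cohort as a whole.

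The conclusion rests on the projected 50 000, on the two assumed rates and on independence. Clustering within centres would widen both intervals.

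**What to change.** Text changes only:

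1. In the Sample size calculation section, say which precision criterion governs. If it is 0.9–1.1% at 1%, give its size as about 41 800 for both Wilson limits, or point to the 9.5% row (42 215). Do not insert 38 100 as a size that guarantees the interval.
2. Replace 105 000 as the operative size by the precision expected at the decided stop: at about 50 000 cases, 0.92–1.09% at 1% and 0.44–0.57% at 0.5%, before allowance for clustering. Keep 105 000 on record as the size for the 0.5% scenario, which will not be reached if the projection holds.
3. Align the abstract (Methods and Results), the Sample size calculation section and the Statistical analysis section with the decision in the Results section. The option to extend or close can stay as the rule under which the decision was made, with a statement that it has been exercised.
4. Delete the age-group qualifier from "we assumed an expected event rate between 1% and 0.5% for the less represented age groups", or state that Table 2's precision applies to the whole cohort and not within age groups.

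The cost is rewording and a less favourable statement of precision. No further patients are needed, and neither data collection nor analysis changes.

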### Statistical analysis

A descriptive analysis of the data will be carried out, using counts and percentages to summarise categorical data and median (interquartile range) to summarise continuous data.

The incidence of critical events will be estimated and reported together with a 95% confidence interval. Furthermore, critical event incidence will be provided for different age categories, operator’s experience, operator’s speciality, and centre volume.

In terms of risk factor analysis, a univariable and multivariable mixed-effect logistic regression model will be computed based on possible predictors, which include for example age (≤12 months), weight (≤10 kg), number of attempts (more than two), presence of comorbidities (ASA score ≥3), comorbidity related to airway management (e.g. relevant syndromes), expected difficult intubation, type of anaesthesia induction (i.v. or inhalation), no neuromuscular blocking agent given, airway surgery or ears, nose, throat (ENT) surgery, and experience level of the person performing tracheal intubation. Appendix 1 lists the relevant factors used for primary and secondary analyses. Goodness-of-fit, calibration, discriminatory capacity, and predictive skill of the regression models will be assessed using Nagelkerke pseudo-*R*^2^, calibration belts, area under the receiver operating characteristic curve (AUROC), and Brier Score, respectively.

The target sample size for CRICKET is informed by statistical considerations and the practical constraints of conducting a large, multinational observational study. Although the sample size calculation indicates that approximately 105 000 cases are required to estimate an event rate of 0.5–1% with acceptable precision, the achievable enrolment also depends on centre capacity, case volume, and the coordinated activation of participating sites across multiple jurisdictions. Recruitment will therefore proceed sequentially from January 2024 to December 2025, with each centre contributing a consecutive 3-month sampling window once local approvals and resources are in place. If the required sample size is not reached by the end of 2025, the steering committee may extend the recruitment period or, alternatively, close enrolment and proceed with analysis of the accrued data, depending on the number of events captured and the resources remaining.

Missing data will be characterised according to recognised mechanisms: missing completely at random (MCAR), where the probability of missingness is unrelated to patient characteristics or outcomes; missing at random (MAR), where missingness depends on observed data; and missing not at random (MNAR), where missingness is related to unobserved factors. We will first explore patterns of missingness to determine the most plausible mechanism. For MCAR or MAR data, we plan to apply appropriate imputation strategies, such as multiple imputation using chained equations, to minimise bias and preserve statistical power. If data are suspected to be MNAR, we will conduct sensitivity analyses to assess the robustness of our findings under varying assumptions about missing values. These procedures will follow best practices for handling missing data in large-scale observational studies. If no imputation is decided, analyses will be performed within the framework of a complete case analysis.

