**Clinical trial registration:**

ClinicalTrials.gov (NCT 05804188).

Tracheal intubation-associated events (TIAEs) can lead to immediate life-threatening complications and long-term sequelae, especially for very young patients and those affected by comorbidities.^1^^,^^2^ The fourth National Audit Project (NAP4)^3^ in the UK estimated that major complications during airway management occur with an incidence of up to 1 in 5500 anaesthesia cases in adults and children. In this audit, the few reported cases with a ‘cannot intubate cannot oxygenate’ (CICO) situation had very severe consequences (death, brain damage, prolonged hospitalisation, unplanned ICU admission). The APRICOT study^4^ reported an incidence of difficult airway, defined as Cormack–Lehane (CL) grading of 3 or 4 or three or more attempts to insert the tracheal tube, of 0.9%, increasing in neonates to 5%, with 40% of these patients suffering from hypoxemia and 8% from hypoxemia and bradycardia. Fortunately, only a small number of severe TIAEs led to long-term morbidity or increased mortality. This low rate of serious sequelae mirrors findings from NECTARINE^5^ and PeDI,^1^^,^^6^ and likely reflects the benefits of early recognition and timely intervention.

Infants and children experience a higher rate of airway-related critical events owing to age-dependent anatomical and physiological features, and syndromic conditions and comorbidities. Therefore, they deteriorate rapidly if not expertly managed. Human factors and variable team performance further influence outcomes, underscoring why current guidelines^2^^,^^7^^,^^8^ advocate limiting attempts, seeking help early, and structured debriefing. Despite these recommendations, practice remains heterogeneous. The Critical Events in Anaesthetised Kids undergoing Tracheal Intubation (CRICKET) study is therefore crucial, providing contemporary, real-world data on paediatric airway management, identifying where gaps persist, and defining priorities to enhance safety and reduce preventable harm.

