## Methods

The primary aim is to determine the incidence of paediatric patients presenting with critical events associated with tracheal intubation. Table 1 presents definitions of critical events used in this study. As an observational study, CRICKET remains inherently susceptible to confounding by indication, although its large sample size and detailed, standardised data collection will help to characterise and mitigate this potential bias. Analysis of these events will focus on identifying clusters of events and risk factors for frequently occurring events. For example, in some conditions, critical events might be characterised by two or more airway-related complications occurring in close temporal proximity during the same intubation episode, suggesting a connected cascade (such as desaturation followed by bradycardia and hypotension) rather than isolated, unrelated events. Similarly, clusters of particular events might be identified in a specific subgroup of patients. This may allow us to identify independent risk factors and, consequently, children at particular risk for critical events.

**Table 1 tbl1:** Definition of critical events associated with tracheal intubation. CPAP, continuous positive airway pressure.

Definition of tracheal intubation-associated critical events	
‘Critical events’ in this study and time frame	Any episode of occurrence during tracheal intubation requiring a medical intervention from the start of anaesthesia until the end of anaesthesia (defined as handover to either the PACU, the paediatric or neonatal intensive care unit, the ward, or discharge home straight from anaesthesia care).
Severe hypoxemia	SpO_2_ <85% or >20 points below initial value for at least 60 s.
Severe bradycardia	Persistent bradycardia for at least 1 min: • 0–3 months old: HR <80 beats min^−1^ • 4 months–2 yr: HR <60 beats min^−1^ • 2–10 yr old: HR <40 beats min^−1^ • 10–16 yr old: HR <30 beats min^−1^
Oesophageal intubation	Tracheal tube placed in the oesophagus diagnosed by (video-) laryngoscopy, absence of sustained EtCO_2_ trace, absence of lung ventilation (auscultation or absence of chest excursions) causing a decrease in oxygenation.

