### Study population and eligibility criteria

Patients are eligible if they fit the following inclusion criteria:•All paediatric patients, aged 0–16 yr, requiring tracheal intubation, either planned or unplanned, performed by the anaesthesia team for procedures or interventions requiring general anaesthesia.•Cases in which a surgeon performs the intubation, whether electively or as a rescue, will be included. Likewise, patients who already have an airway in place (e.g. tracheostomy or tracheal tube) and subsequently undergo airway removal followed by a new intubation will also be captured.

Exclusion criteria are as follows:•Patients >16 yr.•Patients admitted to the operating room already intubated and not requiring a tube exchange.•Refusal to give consent or withdrawal of consent if such is required by the relevant ethics committee.

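### Age (≤12 months) and weight (≤10 kg) as overlapping yes/no predictors cannot separate neonates from older infants and may leave modest residual confounding by age

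*Protocol article*

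**What the plan says.** The Statistical analysis section states that "a univariable and multivariable mixed-effect logistic regression model will be computed", "based on possible predictors, which include for example age" and several others. Four of these are printed with their cut-points: "age (≤12 months), weight (≤10 kg), number of attempts (more than two), presence of comorbidities (ASA score ≥3"). Age and weight are thus two separate binary terms. The text gives no continuous term, no finer banding and no handling of their overlap. It adds that "Appendix 1 lists the relevant factors used for primary and secondary analyses"; that appendix is not shown.

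Four other places bear on the choice:
- Study population and eligibility criteria: "All paediatric patients, aged 0–16 yr, requiring tracheal intubation". The single age cut therefore spans 16 years.
- Introductory text: difficult airway at an incidence "of 0.9%, increasing in neonates to 5" per cent.
- Table 1 in Methods uses four age bands for severe bradycardia, beginning with "0–3 months old: HR <80 beats" per minute.
- Methods gives the purpose of the analysis: to "identify independent risk factors and, consequently, children at particular risk for critical events".

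Separately, the Statistical analysis section plans to report incidence by age category. The cut-points of those categories are not given.

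**The concern.** A cut at 12 months gives all infants the same age coefficient. If risk falls steeply during the first year, the model averages a high neonatal risk with a much lower risk in late infancy and shows neither. Adding weight ≤10 kg does not help, because neonates and almost all younger infants fall on the same side of both cuts. The second indicator mainly picks out heavier infants and lighter toddlers.

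Two further consequences follow. The indicators compete for the same signal, so precision is lost and part of the age effect can appear under weight. And where another predictor (ASA class, operator experience, induction type) varies with age inside the two halves, its odds ratio keeps some confounding by age. At stake is the secondary risk-factor analysis, which is meant to show which children are at particular risk.

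**Working it through.** **The plan's own figures.** No figure in the article depends on how age is coded. Its sample size does reproduce: the smallest n with Wilson half-width z/(1+z²/n)·√(p(1−p)/n + z²/(4n²)) ≤ 0.085 × 0.005 is 105 992, against 105 897 in Table 2 (0.1% apart). The coding of age does not change it.

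The cited gradient for difficult airway is 5/0.9 = 5.6 as a risk ratio, or (0.05/0.95)/(0.009/0.991) = 5.8 as an odds ratio, neonates against all children.

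**Assumptions.** The article gives no case mix, growth curve or critical-event gradient by age, so these are assumed:
- Seven age bands (<1, 1–3 and 3–12 months; 1–2, 2–6, 6–10 and 10–16 yr) with shares 3, 4, 11, 12, 30, 20 and 20%, so 18% are ≤12 months.
- Median weight 3.3 kg at birth, 9.6 kg at 1 yr and 12.2 kg at 2 yr, with 13% variation.
- Baseline risk 0.6%; no effect of weight; no centre effect.
- 1,000,000 cases per run, two runs per scenario.

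**Overlap.** The two indicators agree in 95% of children and correlate at 0.85, so the variance inflation is 1/(1 − 0.851²) ≈ 3.6. At the projected 50 000 patients (20 runs, steep gradient), the standard error of the age coefficient is 0.22 with both terms and 0.10 with age alone. Simulations under other assumptions gave correlations of 0.89 and 0.92.

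**Can the model show neonates?** Take the steep gradient, with odds ratios 6, 3, 2, 1.5, 1.2, 1, 1 across the bands, and treat odds as risks:
- Infant average: (0.03×6 + 0.04×3 + 0.11×2)/0.18 = 0.52/0.18 = 2.89.
- Older children: (0.12×1.5 + 0.30×1.2 + 0.20 + 0.20)/0.82 = 0.94/0.82 = 1.15.
- Infants against older children: 2.89/1.15 ≈ 2.5.
- True contrasts with the same reference: neonates 6/1.15 ≈ 5.2; 3–12 months 2/1.15 ≈ 1.7.

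The fitted two-cut model agrees: age 1.80, weight 1.36, product 2.46. It roughly halves the neonatal contrast and overstates the one for 3–12 months. The weight odds ratio of 1.36 is entirely an age effect. It is 1.30–1.32 under the moderate gradient, 1.16–1.17 under the mild one, and 1.01 if risk is flat on each side of 12 months.

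**Residual confounding.** The exposure has a true odds ratio of 1. Its prevalence by band is 60, 35, 20, 13, 10, 10, 10% (strong link); 30, 22, 18, 13, 11, 10, 10% (weak); or 80, 60, 30, 25, 30, 50, 70% (U-shaped).

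| Age gradient (neonatal OR) | Strong: crude | Strong: two cuts | Strong: seven bands | Weak: two cuts | U-shaped: two cuts |
|---|---|---|---|---|---|
| Steep (6) | 1.54 | 1.20 | 1.00 | 1.09 | 1.08 |
| Moderate (4) | 1.38 | 1.13 | 1.00 | 1.05 | 1.04 |
| Mild (2.5) | 1.22 | 1.08 | 1.01 | 1.04 | 1.03 |
| Flat either side of 12 months (2.5) | 1.28 | 1.00 | 1.00 | 1.01 | 1.00 |

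Across all 12 scenarios the seven-band model returned 0.99–1.02, so differences of about 0.02 are simulation noise. For the strong link with the steep gradient, the cuts remove 1 − ln 1.20/ln 1.54 ≈ 58% of the bias on the log scale. For the U-shaped link they remove almost none.

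**The case against.** The strongest reply is that the article does not fix the model. The list is illustrative, Appendix 1 is not shown, and functional form is often settled in a fuller document. This stands in part: finer coding may already exist. But the cuts themselves are printed, so the coding is stated rather than left open, and the text needs correcting if the appendix differs.

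The 0.9% and 5% refer to difficult airway, not to critical events, which are the outcome of this model. This also stands. The figures support expecting a neonatal gradient but do not give its size.

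Incidence by age category may display the neonatal excess. It is descriptive and unadjusted, so it shows a gradient without repairing the adjusted odds ratios. Calibration belts could reveal some misfit, but overall calibration can look acceptable while predictions are wrong within age groups. The planned causal graph selects confounders; it does not set the form in which age enters.

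Stronger readings are tempting and are not supported:
- That the odds ratios for ASA class and operator experience are biased. The article does not say how either varies with age, and the bias is nil if risk is flat on each side of 12 months.
- That a 13-month-old is given the risk of a 16-year-old. A 13-month-old at or below 10 kg carries the weight coefficient; a typical 16-year-old does not.
- That the overlap makes the estimates unusable. A doubled standard error is a loss of precision, and the overlap depends on growth in a worldwide population not described here.
- That ASA should also be split into classes. Nothing examined here bears on that.

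**Conclusion.** The point holds, conditional on the printed coding being used. That the adjusted model cannot distinguish neonates from older infants follows from the coding alone and needs no simulation. It sits badly with the article's emphasis on neonates and with its aim of identifying children at particular risk.

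The other two consequences depend on assumed growth, case mix and gradients. The overlap is large (correlation about 0.85–0.92), and an age effect can be reported as a weight effect. Residual confounding is modest: about 1.00–1.20 for a true odds ratio of 1, with the upper end needing both a steep gradient and an exposure concentrated in the youngest. The simulations omit the centre effect of the planned mixed model. The primary outcome is not touched.

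**What to change.** Before the analysis starts, state for the multivariable model that:
- Age enters as a non-linear continuous term, such as a restricted cubic spline of log age (with a small constant added, because age can be zero), or in bands that separate neonates and young infants.
- Weight ≤10 kg is replaced by weight-for-age or dropped.
- The cuts at 12 months and 10 kg are used in descriptive tables only.

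If Appendix 1 already codes age more finely, the Statistical analysis section should be aligned with it.

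The cost is in presentation: a curve, or several band odds ratios, replaces one simple odds ratio. No new data are needed if exact age and weight are recorded, which the article does not state and should be confirmed. The extra coefficients are affordable. At 50 000 patients, the planning rates of 0.5% and 1% give 250 and 500 events, and a four-knot spline uses three coefficients where the age cut uses one.
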